### 5.3.2 Use in Pregnancy

Helixor® M may have adverse effects on a fetus; therefore, women with a positive pregnancy test at screening will not be eligible for enrollment. If a patient inadvertently

becomes pregnant while on treatment with Helixor® M, the patient will immediately be removed from the study. The study team will contact the patient at least monthly and document the patient's status until the pregnancy has been completed or terminated. The outcome of the pregnancy will be reported to the Sponsor without delay. The outcome must be reported to the Sponsor within 24 hours if the outcome is a serious adverse experience (e.g., death, abortion, congenital anomaly, or other disabling or life-threatening complication to the mother or newborn). If a male patient's partner becomes pregnant on study the pregnancy must be reported to the Sponsor. The study Investigator will make every effort to obtain permission to follow the outcome of the pregnancy and report the condition of the fetus or newborn to the Sponsor.

#### 5.3.3 Use in Nursing Women

It is unknown whether Helixor® M is excreted in human milk. Since many drugs are excreted in human milk, and because of the potential for serious adverse reactions in the nursing infant, patients who are breast-feeding are not eligible for enrollment.

### 5.4 Definition of Dose-Limiting Toxicity (DLT) and Maximum Tolerated Dose (MTD)

Dose limiting toxicities (DLTs) are defined as the following possibly, probably, or definitely related study drug toxicities:

- $\geq$  grade 3 systemic flu-like symptoms,
- Grade 3 or 4 febrile neutropenia
- Grade 3 or 4 thrombocytopenia with bleeding
- $\geq$  grade 3 non-hematologic and grade 4 hematologic toxicities, or
- Death
- Exceptions include
  - Asymptomatic laboratory abnormalities
  - Grade 3 fatigue
  - Grade 3 dermatologic AEs that are considered mild in severity but only considered grade 3 because of  $>30\%$  body surface involvement (rash, pruritus, etc.)
  - Fever, chills rigors, hypertension, hypotension, syncope, or hypoxia that resolve within 24 hours of intervention
  - Diarrhea, nausea or vomiting that resolves to  $<$  grade 3 within 24 hours of intervention
  - Grade 3-4 hyperglycemia or grade 3 hypophysitis where symptoms are controlled on hormone replacement therapy

Patients will be observed for DLTs for 28 days after the first dose of Helixor® M. Patients who experience a DLT will be discontinued from study treatment. Any patient who receives  $< 75\%$  of the scheduled doses during the DLT period but does not experience a DLT will be replaced.

This phase I study will evaluate up to 8 dose levels of Helixor® M as a single agent: 150 mg, 300 mg, 600 mg, 900 mg, 1200 mg, 1500 mg, 1800 mg, and 2000 mg. Dose escalation

will proceed using an accelerated titration design.

Patients will be assigned to a dose level in the order of study entry. The first cohort of 1 subject will receive mistletoe at the 150 mg dose level. One subject will be enrolled in each cohort until a subject experiences a drug-related toxicity of grader 2 or higher, whereupon an additional 2 patients will be enrolled at that dose level. Thereafter, the traditional 3+3 design will be instituted as described below, with 3 or 6 patients treated at this dose level and at all subsequent dose levels depending upon the incidence of DLTs.

| Number of Patients with DLT at a Given Dose Level                      | Escalation Decision Rule of the 3+3 design                                                                                                                                                                                                                                                                                                                                                                                                                  |
|-------------------------------------------------------------------------------|--------------------------------------------------------------------------------------------------------------------------------------------------------------------------------------------------------------------------------------------------------------------------------------------------------------------------------------------------------------------------------------------------------------------------------------------------------------------|
| 0 out of 3                                                                    | Enter 3 patients at the next dose level.                                                                                                                                                                                                                                                                                                                                                                                                                           |
| $\geq 2$                                                                      | Dose escalation will be stopped. This dose level will be declared the maximally administered dose (highest dose administered). Three (3) additional patients will be entered at the next lowest dose level if only 3 patients were treated previously at that dose.                                                                                                                                                                                                |
| 1 out of 3                                                                    | Enter at least 3 more patients at this dose level. 
 
• If 0 of these 3 patients experience DLT, proceed to the next dose level.
 
• If 1 or more of this group suffer DLT, then dose escalation is stopped, and this dose is declared the maximally administered dose. Three (3) additional patients will be entered at the next lowest dose level if only 3 patients were treated previously at that dose.
 
 |
| $\leq 1$ out of 6 at highest dose level below the maximally administered dose | This is generally the recommended phase 2 dose. At least 6 patients must be entered at the recommended phase 2 dose.                                                                                                                                                                                                                                                                                                                                               |

The MTD is defined as the dose level immediately below the dose level at which  $\geq 2$  patients in a cohort (dose level) of 2 to 6 patients experienced a treatment-related DLT.

If MTDs are not determined at the dose of 2000 mg, this will be the dose taken to the expansion phase and no further escalation of dose is planned.

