## 5.5 General Concomitant Medication and Supportive Care Guidelines

In general, concomitant medications and therapies deemed necessary for the supportive care and safety of the subject are allowed, provided their use is documented in the subject records and on the appropriate case report form. If toxicity occurs, the appropriate treatment will be used to ameliorate signs and symptoms [including antiemetics for nausea and vomiting, anti-diarrheals for diarrhea and anti-pyretics (only if  $\geq 39^{\circ}\text{C}$  or lasting more

than 3 days) and anti-histamines for drug fever]. All supportive measures for optimal medical care will be given during the period of study.

There is a possible risk of anaphylaxis and Helixor® M should be administered in a setting where emergency treatment is available. Administration should be immediately discontinued and the appropriate therapy instituted if there is a serious allergic reaction. The patient must be observed in the clinic for at least 30 minutes after the lead in dose and for the first dose of the assigned dose level. Acute reactions (allergic or allergic-like reactions such as generalized itching, hives, rash, swelling of the face or throat, chills, difficulty breathing, shock or spasm of the airways) will be managed using standard therapy for acute drug reactions as per institutional standard of care and reported to the sponsor. If a grade 1 or 2 hypersensitivity reaction is suspected, this must be discussed with the IND sponsor and principal investigator before the patient is given another dose of Helixor® M. Patients developing grade 3 or 4 hypersensitivity will not receive another dose of Helixor® M.

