#### Guidance on Infusion/Hypersensitivity Reactions:

Treatment recommendations are provided below and may be modified based on local treatment standards and guidelines as appropriate:

For grade 1 symptoms (mild reaction; infusion interruption not indicated; intervention not indicated):

Remain at bedside and monitor subject until recovery from symptoms. The following prophylactic premedications are recommended for future infusions: diphenhydramine 50 mg (or equivalent) at least 30 minutes before additional Helixor® M administrations.

For grade 2 symptoms (moderate reaction requires therapy or infusion interruption but responds promptly to symptomatic treatment [e.g., antihistamines, non-steroidal anti-inflammatory drugs, narcotics, corticosteroids, bronchodilators, IV fluids]; prophylactic medications indicated for  $\leq 24$  hours):

Stop the Helixor® M infusion, begin an IV infusion of normal saline, and treat the subject with diphenhydramine 50 mg IV (or equivalent) and/or acetaminophen 325 to 1000 mg; remain at bedside and monitor subject until resolution of symptoms. If the infusion is interrupted, restart the infusion at 50% of the original infusion rate when symptoms resolve; if no further complications ensue after 30 minutes, the rate may be increased to 100% of the original infusion rate. Monitor subject closely. If symptoms recur then no further Helixor® M will be administered at that visit. Administer diphenhydramine 50 mg IV, and remain at bedside and monitor the subject until resolution of symptoms. The amount of study drug infused must be recorded on the case report form (CRF). The following prophylactic premedications are recommended for future infusions: diphenhydramine 50 mg (or equivalent) and/or acetaminophen 325 to 1000 mg should be administered at least 30 minutes before additional Helixor® M administrations.

For grade 3 or grade 4 symptoms (severe reaction, grade 3: prolonged [i.e., not rapidly responsive to symptomatic medication and/or brief interruption of infusion]; recurrence of

symptoms following initial improvement; hospitalization indicated for other clinical sequelae [e.g., renal impairment, pulmonary infiltrates]; grade 4: (life threatening; pressor or ventilator support indicated):

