## **5.6 Duration of Therapy**

In the absence of treatment delays due to adverse event(s), treatment may continue until one of the following criteria applies:

- The patient or legal representative (such as a parent or legal guardian) withdraws consent for treatment
- Disease progression: Patients may be allowed to continue treatment if the Principal Investigator feels that the subject is receiving benefit based on the following criteria:
  - Investigator-assessed clinical benefit, and

- Subject is tolerating study drug.

The assessment of clinical benefit should take into account whether the subject is clinically deteriorating and unlikely to receive further benefit from continued treatment. The following criteria need to be taken into consideration:

- Absence of clinical symptoms and signs indicating disease progression.
- No decline in ECOG performance status.
- Absence of rapid progression of disease or of progressive tumor at critical anatomical sites requiring urgent alternative medical intervention.

All decisions to continue treatment beyond PD must be discussed with the Principal Investigator.

- Intercurrent illness that prevents further administration of treatment,
- DLT listed in **Section 5.4**,
- Grade 3 or 4 Helixor® M hypersensitivity reaction,
- Treatment delays lasting longer than 2 weeks due to a drug-related toxicity that does not resolve to a  $\geq$  grade 1 or baseline despite supportive treatment per standard clinical practice,
- If in the opinion of the Investigator, a change or temporal or permanent discontinuation of therapy would be in the best interest of the patient,
- Noncompliance with trial treatment or procedure requirements,
- Patient is lost to follow-up, or
- Patient becomes pregnant.

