## **6. DOSING DELAYS AND SCHEDULING/DOSE MODIFICATIONS**

### **6.1 Dosing Delays and Scheduling/Missed Doses**

Helixor® M will be held for drug-related fever  $\geq 39^{\circ}\text{C}$ , chills, transient dizziness, or if the dosing criteria per **Section 5.2** are not met. If a delayed dose cannot be made up during the same week, it will be skipped. If toxicity does not resolve to  $\leq$  grade 1 or baseline within 2 weeks, trial treatment should be discontinued after consultation with the IND sponsor and principal investigator.

Patient-initiated, pre-planned missed doses (for example, due to vacation plans) are not permitted during the first 8 weeks of treatment. Missed doses due to clinic scheduling and holiday closures are permitted. Patients are allowed to move 1 treatment per week by 1 day (for example: MWF  $\rightarrow$  TWF). Helixor® M infusions may not be given less than 24 hours apart. In special cases, after a documented discussion with the PI, Helixor® M infusions may be given on three consecutive days (for example: MTW) as long as they are given at least 24 hours apart. Up to 3 missed doses of Helixor® M for every 12 doses will be permitted after week 8. Allowance of Helixor® M breaks of greater than 1 week will be decided on a case-by-case basis by the Principal Investigator.

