## **7. ADVERSE EVENTS: LIST AND REPORTING REQUIREMENTS**

This study will use the descriptions and grading scales found in the revised National Cancer Institute Common Terminology Criteria for Adverse Events (CTCAE) Version 4.03 for adverse event reporting that can be found at [http://ctep.cancer.gov/protocolDevelopment/electronic\\_applications/ctc.htm](http://ctep.cancer.gov/protocolDevelopment/electronic_applications/ctc.htm).

The Investigator or designee must completely and promptly record each adverse event using the CRF, regardless of relationship to study drug as determined by the Investigator. The Investigator should attempt, if possible, to establish a diagnosis based on the patient's signs and symptoms. When a diagnosis for the reported signs or symptoms is known, the Investigator should report the diagnosis, not the symptoms, as the adverse event.

Information about all adverse events, whether volunteered by the subject, discovered by investigator questioning, or detected through physical examination, laboratory test or other means, will be collected, recorded, and followed as appropriate.

All adverse events experienced by patients will be collected and reported from the first dose of the investigational agent, throughout the study, and will only be followed for 28 days after the maximal planned dose is administered unless there are ongoing problems thought to be related to the investigational agent.

Patients who have an ongoing adverse event related to the study procedures and/or medication(s) may continue to be periodically contacted by a member of the study staff until the event is resolved or determined to be irreversible by the investigator.

**Laboratory abnormalities:** Laboratory abnormalities present at the screening visit will be recorded as pre-treatment signs and symptoms. After study treatment administration, all grade 3 and 4 clinical laboratory results that represent an increase in severity from baseline will be reported as adverse events. A grade 1 or 2 clinical laboratory abnormality should be reported as an adverse event only if it is considered clinically significant by the investigator.

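### The 24-hour DLT exception in Protocol 5.4 has no grade cap, so a related grade 4 hypertension, hypotension or hypoxia that is not diagnosed as an infusion or hypersensitivity reaction need not count as a DLT

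*Protocol*

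**What the plan says.** Section 5.4 lists the DLT criteria for toxicities possibly, probably or definitely related to study drug. The general one covers, from the stated grade upward, "grade 3 non-hematologic and grade 4 hematologic toxicities". Flu-like symptoms of grade 3 or higher have their own line. A list of exceptions follows, including "Fever, chills rigors, hypertension, hypotension, syncope, or hypoxia that resolve within 24 hours of intervention". That line carries a time limit and no grade.

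The other exceptions vary. Fatigue and extensive but mild skin events are exempt at grade 3 only. One line names grade 4 openly: "Grade 3-4 hyperglycemia or grade 3 hypophysitis where symptoms are controlled" on hormone replacement. Diarrhea, nausea and vomiting are exempt if they fall below grade 3 within 24 hours, with no upper grade.

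Section 5.5 deals with reactions to the drug. "Patients developing grade 3 or 4 hypersensitivity will not receive another dose of Helixor® M". Its guidance covers infusion reactions as well as hypersensitivity, describes grade 4 as "life threatening; pressor or ventilator support indicated", and says that the drug is permanently discontinued after grade 3 or 4.

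Section 5.6 ends treatment for a DLT listed in 5.4 or a grade 3 or 4 hypersensitivity reaction, and otherwise allows a stop as follows: "If in the opinion of the Investigator, a change or temporal or permanent discontinuation of therapy would be in the best interest of the patient". Section 6.1 begins its hold list with "Helixor® M will be held for drug-related fever" of 39 °C or more, then chills, transient dizziness and failed dosing criteria. Those criteria (5.2) are laboratory values. Section 7 adds that, when a diagnosis is known, "the Investigator should report the diagnosis, not the symptoms, as the adverse event".

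**The concern.** A DLT exception for transient events makes sense for a drug expected to cause fever and chills. Hypotension, hypertension and hypoxia differ, because at grade 4 a circulatory or respiratory event can be immediately life threatening. It may be reversed within 24 hours because emergency treatment was given, so quick reversal does not show that the dose is tolerable.

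The DLT count decides escalation and the MTD (5.4, 13.1), and a DLT obliges the patient to stop (5.4, 5.6). An exempted grade 4 event would do neither. Whether a given episode counts would also depend on how it is labelled: as an infusion reaction it is a DLT, as isolated hypotension it is not. In a multi-center trial, sites may label it differently.

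**Working it through.** **Step 1. Does any other text restore the event as a DLT?** Take a related grade 4 hypotension, reversed within 24 hours of intervention. The protocol grades by CTCAE 4.03 without reproducing it; the argument needs only that these events can be graded 4.

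| How the event is recorded | Is it a DLT? | Must the patient stop? |
|---|---|---|
| Grade 3–4 infusion or hypersensitivity reaction | Yes: non-hematologic, grade 3 or higher, not in the exception list | Yes: 5.4, and 5.5 (permanent discontinuation) |
| Part of flu-like symptoms of grade 3 or higher | Yes: separate line in 5.4 | Yes: 5.4 |
| Isolated hypotension | No: exempt on time to resolution | No: not a DLT under 5.6 and not on the 6.1 hold list; left to investigator judgment |

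Section 13.1 has no separate list of DLT toxicities. The rule that a related event of grade 2 or higher ends single-patient cohorts still applies and adds 2 patients at that dose, but does not make the event a DLT. Only the third row is open.

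**Step 2. Effect on the 3+3 count** (rules from 5.4 and 13.1).

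- Only severe event in a cohort of 3: exempted, 0 of 3, so escalate; counted, 1 of 3, so 3 more patients at the same dose.
- One other DLT in the cohort: exempted, 1 of 3, so 3 more patients, and escalation follows if none of them has a DLT; counted, 2 of 3, so escalation stops.

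Dose step = next dose / current dose − 1:

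| Step (mg) | Increase |
|---|---|
| 150 to 300 | 100% |
| 300 to 600 | 100% |
| 600 to 900 | 50% |
| 900 to 1200 | 33% |
| 1200 to 1500 | 25% |
| 1500 to 1800 | 20% |
| 1800 to 2000 | 11% |

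**Step 3. Effect on the expansion rule.** Section 13.1 uses a beta(2, 5.5) prior and suspends enrollment when P(rate > 0.3) is at least 0.75. With x events in n patients:

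P = 1 − BetaCDF(0.3; 2 + x, 5.5 + n − x)

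| n | One event below boundary | At boundary |
|---|---|---|
| 2 | 1: 0.506 | 2: 0.769 |
| 3 | 2: 0.690 | 3: 0.877 |
| 4 | 2: 0.609 | 3: 0.821 |
| 5 | 2: 0.531 | 3: 0.757 |
| 6 | 3: 0.689 | 4: 0.859 |
| 7 | 3: 0.619 | 4: 0.808 |
| 8 | 3: 0.550 | 4: 0.752 |
| 9 | 4: 0.691 | 5: 0.848 |
| 10 | 4: 0.628 | 5: 0.801 |

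The right-hand column reproduces the protocol's boundary exactly (2 of 2; 3 of 3–5; 4 of 6–8; 5 of 9–10), so the boundary itself is correct. One uncounted event can separate continuing from suspending, but that is true of any integer boundary and any uncounted event. The table does not measure how much this exception matters.

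What the rule counts is also unclear. Section 13.1 speaks of toxicities meeting DLT criteria, then bases the prior on an expected SAE rate and labels the table by AEs. On the DLT reading an exempted grade 4 event is missed. On the AE or SAE reading it is counted, since a life-threatening event is an SAE under 7.1.2.

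**The case against.** The strongest reply is that the event that matters most is already covered. A grade 4 circulatory collapse or hypoxia around a 3-hour infusion would usually be called an infusion reaction. Section 5.5 then discontinues the drug, Section 7 tells the investigator to report the diagnosis, and the diagnosis is not exempt. This largely stands, and it is why the point is limited to events not so diagnosed. It does not close the gap: the treatment guidance in 5.5 may be modified to local standards, 5.6 names only hypersensitivity, and the outcome depends on the label.

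It can also be said that the missing cap fits the list, since hyperglycemia is exempt to grade 4 and the gastrointestinal line has no ceiling. That is true, and exempting by duration may be deliberate. But the protocol gives no reason for exempting grade 4 hypotension, hypertension or hypoxia.

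Thirdly, the listed IV reactions (2.1, 7.6) are mainly allergic, febrile or local. Isolated hypotension, hypertension and hypoxia are not among them, so nothing shows that the scenario is likely. This stands. So do the other safeguards: the grade 2 trigger, SAE reporting within 24 hours, bi-weekly safety meetings and Safety Monitoring Committee oversight. None of them adds the event to the DLT count.

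A reader might infer that any rapidly reversed life-threatening reaction to the drug escapes the DLT rules and that dosing continues. The documents do not support that, because diagnosed grade 3 or 4 reactions count and end treatment. Nor do they support a flat statement that the expansion rule ignores such events, given its mixed wording.

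**Conclusion.** The point holds in a narrow form. As 5.4 is written, a related grade 4 hypertension, hypotension or hypoxia that is reversed within 24 hours and not diagnosed as an infusion or hypersensitivity reaction, or as flu-like symptoms of grade 3 or higher, is not a DLT. No other section changes that. The consequence is one missing DLT in the 3+3 count, which can permit the dose steps shown above, and no mandatory stop for that patient. An effect on expansion monitoring follows only if that rule counts DLT-criteria events alone.

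The conclusion rests on the wording and on no assumed event rate, so the chance that it alters the MTD is unknown and may be small. The change is still worth making: safety and the MTD are the primary objectives, and the correction is cheap.

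**What to change.** In 5.4, start the exception with *Grade 3*, so that it exempts only transient grade 3 events of the listed types, and add after it: *any related grade 4 event of these types is a DLT*. The 24-hour condition stays as it is. The change does not touch the uncapped gastrointestinal exception and does not define the grade to which an event must resolve.

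The cost is one line of amendment and no added procedures. An occasional extra DLT may add 3 patients to a cohort, stop escalation earlier or suspend expansion enrollment sooner, and the patient concerned must stop treatment.
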